### 7.3.6 FACIT-Score

The minimal clinically important difference in patients with SLE for the FACIT-Fatigue is between 3 and 4 points and will also be used in this clinical trial [81, 82].

### 7.3.7 GLUCOCORTICOID DOSAGE

In this study, tapering of the glucocorticoid dosage administered for the indication SLE is allowed after Week 12 (primary end point visit), if justified according to the judgment of the treating physician (See section 6.4.1 GLUCOCORTICOID THERAPY). This allows investigating the steroid sparing effect of the study drug, and steroid reduction is one of the secondary endpoints, as advocated by leading experts in managing lupus [83]. The glucocorticoid dosage must be stable until Week 12 and may be tapered thereafter. The average reduction of oral glucocorticoid will be analyzed at baseline, and follow-up visits of the core study period at Week 3, 5, 7, 9, 12, 16, 20, 24, 28, 32 and 36, and Week 42, 48, 54, 60, 66, 72, 78 and 84 of the LTE observational period.

### 7.3.8 SLICC Damage Index (SDI)

The change in accumulating organ damage will be investigated using the ACR/SLICC Damage Index (SDI). The SDI was developed to quantify damage that has occurred since onset of lupus. It has been shown to be a valid measure for damage and correlates with mortality. In this index, damage is defined a non-reversible change, not related to active inflammation, occurring since the onset of lupus, ascertained by clinical assessment and present for at least 6 months

## 7.4 PHARMACODYNAMICS

Pharmacodynamic (PD) markers monitoring the biological effect of the study drug will be evaluated primarily by flow cytometry focusing on the number and phenotype of immune cell subsets. They include analysis of peripheral blood plasmacytoid dendritic cells (pDCs), natural killer (NK) cells, CD4+ and CD8+ T cells, CD19+ B cells and CD19+CD20negCD27high plasmablasts, including their surface expression of CD38. For this reason, peripheral blood mononuclear cells (PBMC) from 30ml heparinized blood will be isolated by density centrifugation and cryopreserved before analysis in the research facilities of German Rheumatism Research Center (DRFZ Berlin, a Leibniz Institute, Berlin, Germany). In addition, change from baseline in interferon type I activity, and lymphocyte typing (cellular status), will be investigated on freshly isolated PBMC from 2x2ml heparinized blood and investigated in the local laboratory "LaborBerlin". Finally, change from baseline in gene expression profile and antigen receptor repertoire on peripheral blood T and B cells will be investigated. To this end, isolated PBMC from 20ml heparinized blood will be isolated at baseline and at Week 9 and cryopreserved before analyses by single-cell RNA sequencing and receptor repertoire analysis, which

will be performed at the German Rheumatism Research Center (DRFZ Berlin, a Leibniz Institute, Berlin, Germany).

## 7.5 PHARMACOKINETICS

Daratumumab concentrations will be analyzed after the end of the study from cryopreserved serum samples, which had been obtained at Week 9 (one week after the last daratumumab injection), under the premise that the primary endpoint will be achieved. For this reason, a serum sample (5ml serum tube) will be cryopreserved for later analysis.

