### 3 OBJECTIVES, ENDPOINTS, AND HYPOTHESIS OF THE STUDY

#### 3.1 OBJECTIVES

##### 3.1.1 PRIMARY OBJECTIVE OF THE CORE STUDY PERIOD

The primary objective of this study is to evaluate whether treatment with eight weekly subcutaneous injections of daratumumab is associated with a significant reduction of pathogenic serum anti-dsDNA antibodies in patients with moderate to severe SLE.

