### 3.1.3 ADDITIONAL OBJECTIVES OF THE CORE STUDY PERIOD

1. Investigate pharmacodynamic markers (e.g. number and phenotype of peripheral plasmablasts/plasma cells, NK cells, T and/or B cell subsets, including their expression levels of CD38, type-I interferon activity), gene expression analysis and receptor repertoire changes in T and B cells
2. Investigate study drug concentration in serum (only if primary endpoint is achieved)

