## 3.2 ENDPOINTS

### 3.2.1 PRIMARY ENDPOINT OF THE CORE STUDY PERIOD

The primary endpoint is the reduction of serum anti-dsDNA antibody titers after 8 repeated weekly injections of daratumumab at Week 12, i.e. 4 weeks after the last daratumumab injection, compared to baseline.

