### 3.2.4 ADDITIONAL ENDPOINTS OF THE CORE STUDY AND LTE OBSERVATIONAL PERIOD

1. Immunologic changes (pharmacodynamics) following daratumumab treatment will be evaluated as follows:

- Change from baseline in number and phenotype of peripheral blood plasmacytoid dendritic cells (pDC), natural killer (NK) cells, CD4+ and CD8+ T cells, CD19+ B cells and CD19+CD20negCD27high plasmablasts, by visit. Immunophenotyping will be performed by multicolor flow cytometry including expression analysis of CD38 on immune cell subsets by using an anti-CD38 multipeptide antibody that binds to an epitope distinct from the epitope bound by daratumumab. Time frame: baseline, and follow-up visits of the core study period at Week 3, 5, 7, 9, 12, 16, 20, 24, 28, 32, 36, and at Week 42, 48, 54, 60, 66, 72, 78 and 84 of the LTE observational period.
- Change from baseline in interferon type I activity, by visit, Time frame: up to Week 36. Type I interferon activity is a hallmark of SLE; it will be measured by analyzing its surrogate parameter SIGLEC-1 (CD169) on monocytes by flow cytometry. Time frame: baseline, and follow-up visits of the core study period at Week 3, 5, 7, 9, 12, 16, 20, 24, 28, 32, 36, and at Week 42, 48, 54, 60, 66, 72, 78 and 84 of the LTE observational period.  
Change from baseline in gene expression profile and antigen receptor repertoire on peripheral blood T and B cells. Time frame: week 9 (one week after the last daratumumab injection). Transcriptomic profiling will be performed using single-cell RNA sequencing (scRNA-Seq) combined with T cell receptor (TCR) and B cell receptor (BCR) analysis in peripheral blood CD4+ and CD8+ T cell and CD19+ B cell subsets. Time frame: baseline and follow-up visit of the core study period at Week 9, and at the entry visit in the LTE observational period.

2. Pharmacokinetics will be investigated as follows:

- Daratumumab concentrations will be analyzed after the end of the study from cryopreserved serum samples, which had been obtained at Week 9 (one week after the last daratumumab injection), provided that the primary endpoint will be achieved. Time frame: Week 9 of the core study, and at entry visit in the LTE observational period.

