### 9.5 EFFICACY ANALYSES

#### 9.5.1 PRIMARY ENDPOINT ANALYSIS

The median and interquartile range (25th centile – 75th centile) is reported for anti-dsDNA antibody titers at baseline and at Week 12, i.e. 4 weeks after the last daratumumab injection. The change in between the two assessments is not tested in a confirmatory manner because of the exploratory study design. The median change is reported with its 95% confidence interval.

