### 9.7 PHARMACOKINETIC ANALYSES

The daratumumab concentration will be investigated after the end of the study from cryopreserved serum samples obtained at 1 week after the last daratumumab injection, i.e. Week 9, provided that

the primary endpoint is achieved, and at study entry in the LTE observational period. Descriptive statistics will be used to report the study drug concentration.

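### Daratumumab concentrations are assayed only if the primary endpoint is 'achieved', a trigger the protocol never defines and one that drops on-treatment exposure data when titres do not fall

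*Protocol*

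**What the plan says.** The condition appears five times in the protocol: in the synopsis (additional objectives), in 3.1.3, in 3.2.4 ("provided that the primary endpoint will be achieved"), in 7.5 ("under the premise that the primary endpoint will be achieved") and in 9.7. Section 7.5 has a Week 9 serum sample frozen for every patient and analysed after the study ends. The draw and the storage are therefore unconditional, and only the assay depends on the outcome.

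The event it depends on is described in three places:

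- Section 3.2.1 defines a continuous quantity: "The primary endpoint is the reduction of serum anti-dsDNA antibody titers after 8 repeated weekly injections of daratumumab at Week 12", compared with baseline.
- Section 3.1.1 asks whether treatment "is associated with a significant reduction of pathogenic serum anti-dsDNA antibodies in patients with moderate to severe SLE", and attaches no rule to that adjective.
- Section 9.5.1 makes the analysis descriptive: "The change in between the two assessments is not tested in a confirmatory manner because of the exploratory study design". It adds: "The median change is reported with its 95% confidence interval".

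The Wilcoxon signed-rank test is named only in the sample-size text (9.2 and synopsis).

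The LTE-entry concentration sample is included in 3.2.4, in 9.7 ("the primary endpoint is achieved, and at study entry in the LTE observational period") and in the LTE schedule of 7.1.1. Section 7.5 does not mention it, and the front-matter LTE schedule has no pharmacokinetics row.

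**The concern.** There are two problems, and they are separate.

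First, the protocol uses a success event as a trigger without saying what success is. A continuous change summarised by a median and an interval is not achieved or missed until someone adds a rule. As written, that rule could be chosen after the titres are known.

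Second, the condition points the wrong way. Section 2.2 presents the trial as a proof of concept that the drug acts on plasma cells in lupus. The two earlier lupus patients were treated intravenously (2.1.4.5). This trial uses a fixed subcutaneous dose (6.2.1), and the subcutaneous exposure data cited come from myeloma (2.1.4.3). Skipped doses are not made up (6.2.4). If titres do not fall, one of the first questions is whether patients had adequate exposure. In that case the plan cancels the one planned concentration measurement taken close to treatment.

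**Working it through.** **1. Is a rule for 'achieved' given anywhere?** Sections 3.2.1 and 7.3.1 name the quantity and give no cut-off. Section 3.1.1 says significant but names no test. Section 9.2 names a test, but only to size the trial. Section 9.5.1 gives an interval but attaches no decision to it. None of these is linked to the assay condition.

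**2. The plan's own figure.** From 9.2, effect size = 250/121 = 2.066 (stated as 2.1), two-sided 5%, 80% power. A noncentral-t calculation with the usual efficiency adjustment for the Wilcoxon test gives:

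- adjustment 3/π: power 0.738 at n = 4 and 0.902 at n = 5;
- adjustment 0.864 (the minimum): power 0.639 at n = 4 and 0.840 at n = 5.

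Five is therefore the smallest n reaching 80%, and 5/(1 − 0.5) = 10. The stated 5 and 10 reproduce and are not in dispute.

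**3. Does the choice of reading matter?** Three readings at n = 10, with no true effect:

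- *Any median reduction*: 50%, by symmetry.
- *Exact two-sided Wilcoxon p ≤ 0.05, in the direction of a reduction*: 2.4% (exact enumeration).
- *Order-statistic interval for the median excludes zero*: the interval from the 2nd to the 9th ordered change covers 97.9%. It lies wholly on the reduction side when at most one patient fails to fall: (1 + 10)/1024 = 1.1%.

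The rows for a true effect come from simulation (100,000 runs). The normal changes and the smaller effect sizes are assumptions, because the protocol gives only the planning value.

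| True mean reduction (SD of change) | Any median fall | Wilcoxon | Interval excludes 0 |
|---|---|---|---|
| 0 | 50% | 2.4% | 1.1% |
| 0.3 | 79% | 13% | 6% |
| 0.5 | 91% | 28% | 14% |
| 1.0 | 99.7% | 79% | 51% |
| 2.07 (planning value) | 100% | 100% | 98.5% |

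At the planning effect the readings agree. They diverge where the result is modest or absent, which is where the decision to assay would be in doubt.

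**4. Can the LTE-entry sample replace Week 9?** The core schedule puts the last dose at day 49, Week 9 at day 56 and Week 36 (LTE entry) at day 241. Week 9 is 56 − 49 = 7 days after the last planned dose. LTE entry is 241 − 49 = 192 days after it, or later for patients who join late. It says little about exposure during treatment.

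**The case against.** **A usable reading exists.** An interval excluding zero in the direction of reduction is a natural meaning of the condition, and a statistical analysis plan could fix it. That is fair, so the trigger is better called ambiguous than impossible to evaluate. But the protocol itself sets the trigger, and no definition of success cures its direction.

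**A negative trial would not be blind on exposure.** Site staff give every dose and record times and volume (6.3). Immune-cell subsets and CD38 expression are measured whatever the outcome, with a reagent that binds elsewhere on CD38 than the drug does (3.2.4, 7.4). Immunoglobulins and vaccine titres are also followed (3.2.3). This stands in part. These data show that the drug was given and what it did, but not how much was in serum.

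**It is a resource choice.** Pharmacokinetics is an additional objective with descriptive reporting, and the condition is disclosed in advance. This is also fair, and it limits the weight of the point.

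Three stronger readings are tempting, and the documents do not support them:

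- *That the assay would never be run.* With exactly five non-zero changes, the smallest two-sided Wilcoxon p is 2/2^5 = 0.0625. But five is the pre-dropout planning figure. The main analysis includes all enrolled patients (9.3), carries the last value forward (9.4) and keeps patients who stop the drug in the study (8.2). The minimum is 2/2^6 = 0.031 at n = 6 and 2/2^10 = 0.002 at n = 10. It is a worst case of one reading, using a test that the primary analysis does not apply.
- *That a negative trial would certainly have exposure data on none of its 10 patients.* Section 9.7 can be read as leaving the LTE-entry sample unconditional, and the frozen Week 9 serum would still exist.
- *That exposure would be reported on a selected outcome.* The condition acts on the whole trial: all samples are assayed or none. Responders are not picked out.

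**Conclusion.** The point holds as a cheap improvement. The assay of the Week 9 samples hangs on a word that the protocol ties to no threshold, test or interval rule. Depending on the reading, the chance of assaying when the drug has no effect on titre runs from about 1% to 50% at n = 10; with an assumed effect of 0.5 SD it runs from about 14% to 91%. The ranges assume all 10 patients contribute a change, and the non-null figures also assume normal changes.

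The direction of the condition matters more than its ambiguity. Followed as written, the plan gives up on-treatment concentrations when they would be most informative. That is a judgement about the purpose of a proof-of-concept trial and does not depend on the arithmetic. The loss is partial, because dosing records and pharmacodynamic markers remain, and it is reversible for as long as the serum is kept. The primary analysis is not affected.

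**What to change.** Delete the condition in the synopsis, 3.1.3, 3.2.4, 7.5 and 9.7. State that all stored Week 9 samples are assayed whatever the titre result, and that concentration is reported descriptively alongside each patient's change in anti-dsDNA titre. With at most 10 points this is a display, not an exposure-response analysis.

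As housekeeping, bring 7.5 and the front-matter LTE schedule into line with 3.2.4, 9.7 and the LTE schedule in 7.1.1, which already include the LTE-entry sample.

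The cost is protocol wording and at most 10 extra Week 9 assays, on serum that the plan already draws and freezes. No visit, blood draw or treatment changes.

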## 7.6 SAFETY EVALUATIONS

Safety evaluations during this study include the assessment of AEs, concomitant drugs, pregnancy tests, injection related reactions (IRR), chemical and hematological laboratory tests, immunogenicity, vital signs and physical examinations. If the visit is on-site, a rapid SARS-CoV-2 test will be performed at each study visit. If this result is positive, a PCR SARS-CoV-2 test must follow for confirmation. In addition, screening procedures will include an electrocardiogram (ECG), chest x-ray (in accordance with local regulations), HIV testing, hepatitis B, hepatitis C and TB tests. All AEs and any clinically relevant changes in concomitant diseases occurring during the study must be recorded on the AE section of the CRF. The study will include the following evaluations of safety and tolerability at specific time points, as shown in the flow chart in section 7.1.1.

### 7.6.1 ADVERSE EVENTS

Adverse events will be reported by the subject (or, if applicable, by a caregiver, surrogate) for the duration of the study. In addition to patient reporting on possible AE's, adverse events can also be observed during physical examination or by laboratory tests performed by the physician. Adverse events will be followed by the Investigator as specified in Section 10, Adverse Event Reporting. See also section 10.1. for AE definitions.

### 7.6.2 INJECTION RELATED REACTION and INJECTION SITE REACTIONS

An injection related reaction (IRR) is defined as any adverse reaction that occurs during or short after an application of the study drug. Daratumumab injection solution for subcutaneous application can cause severe and/or serious IRRs, including anaphylactic reactions. Symptoms of IRRs can be respiratory symptoms like stuffy nose, cough, and irritation of throat, allergic rhinitis, wheezing respiration as well as pyrexia, chest pain, itching, chills, vomiting, nausea and hypotension. Severe IRRs that may occur include bronchospasm, hypoxia, dyspnea, hypertension and tachycardia (see also the Investigator's Brochure).

An injection site reaction (ISR) is any adverse event that occurs at or around the injection site and is time-related to the last administration of test drug. Patients should be monitored for the occurrence of injection site reactions and/or generalized allergic reaction. Therefore, subjects need to be observed for 6 hours after the end of first daratumumab dose and if deemed necessary by the investigator after consecutive injections. Permanent discontinuation of study agent must be considered for patients who experience an adverse event of injection reaction that is judged serious or severe by the Investigator, e.g. allergic reaction, anaphylaxis (see also section 8.2 DISCONTINUATION OF STUDY TREATMENT). If the subject experiences a Grade 2 or higher event of laryngeal edema, or a Grade 2 or higher event of

bronchospasm that does not respond to systemic therapy and does not resolve within 6 hours from onset, then the subject must be withdrawn from daratumumab treatment.

Administration of daratumumab may be restarted upon recovery from toxicity to Grade  $\leq 2$  or baseline, apart from laryngeal edema, bronchospasm or febrile neutropenia, which must be fully recovered (see also section 6.2.4 DOSE MODIFICATION AND DELAYS). If a laryngeal edema or bronchospasm occurs, the Sponsor-Investigator must be contacted prior to any further application of daratumumab to discuss and assess the risks and benefits of further exposure to daratumumab in the trial.

### 7.6.3 CLINICAL LABORATORY TESTS

The following laboratory tests will be performed by the local laboratory (unless otherwise specified) and according to the flow chart in chapter 7.1.1:

- Hematology Panel
  - Hemoglobin
  - Hematocrit
  - White blood cell (WBC) count with differential (basophils, eosinophils, lymphocytes, monocytes, neutrophils)
  - Platelet count
- Serology Laboratory
  - Anti-dsDNA antibodies
  - Immunoglobulin isotype profile (IgG, IgM, IgA levels)
  - Serum complement factors C3 and C4
  - Antinuclear antibodies (ANA)
  - Antiphospholipid antibodies, including anti-cardiolipin, anti- $\beta 2$ -glycoprotein and anti-phosphatidylserine antibodies (repeated measurements only if present at baseline)
  - Extractable nuclear antibodies (ENA), including anti-Ro/SSA, anti-La/SSB, anti-ribonucleoprotein (anti-RNP), anti-U1RNP, anti-Sm (repeated measurements only if present at baseline)
  - rheumatoid factor, and anti-cyclic citrullinated peptide (repeated measurements only if present at baseline)
  - anti-Tetanus-Toxoid (TT), anti-Diphtheria and anti-Measles antibody titers
- Serum Chemistry Panel
  - Sodium
  - Potassium
  - C-reactive protein
  - Total protein
  - Creatinine
  - Creatinine kinase
  - Alanine aminotransferase
  - Aspartate aminotransferase
  - NT-Pro BNP
  - total bilirubin, and if total bilirubin is abnormally elevated, then direct bilirubin, and indirect bilirubin
- -Blood bank

- Antiglobulin (Coombs) test at baseline (compatibility testing/crossmatch), and repeated only if pathologic at baseline
- Coagulation Labs
  - Partial Thromboplastin Time
  - Prothrombin Time
  - International Normalized Ratio (INR)
- Urine Analyses – Fresh spot urine
  - Urine dipstick
  - Urine sediment evaluation
  - Urinary protein/creatinine ratio
- Urine pregnancy testing for women of childbearing potential only or serum pregnancy test (at the discretion of the Investigator)
- Viral serology (HBsAg, anti-HBs, and HCV antibody)
- QuantiFERON® -Tuberculosis test

The investigator must review the laboratory results in a timely manner, document, date and sign the results. All clinically relevant changes in laboratory results that occur during the study must be documented as adverse events in the CRF. The laboratory reports must be filed together with the other source documents.

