| SLE classification (2019 EULAR/ACR criteria)      | x         |          |          |    |    |    |    |    |    |    |                     |         |     |     |     |     |                             |
| QuantiFERON-TB                                    | x         |          |          |    |    |    |    |    |    |    |                     |         |     |     |     |     |                             |
| Viral Serology                                    | x         |          |          |    |    |    |    |    |    |    |                     |         |     |     |     |     |                             |
| Screening SLE Serology for SLEDAI-2K              | x         |          |          |    |    |    |    |    |    |    |                     |         |     |     |     |     |                             |
| SLICC Damage Index                                |           | x        |          |    |    |    |    |    |    |    |                     |         |     |     |     |     |                             |
| Study Treatment Administration                    |           |          |          |    |    |    |    |    |    |    |                     |         |     |     |     |     |                             |
| Dispense/administer study drug                    |           | x        | x        | x  | x  | x  | x  | x  | x  |    |                     |         |     |     |     |     |                             |
| Clinical Response Evaluations                     |           |          |          |    |    |    |    |    |    |    |                     |         |     |     |     |     |                             |
| SLEDAI-2K                                         | x         | x        | x        |    | x  |    |    | x  |    | x  | x                   | x       | x   | x   | x   | x   | x                           |
| Physician's Global Assessment of Disease Activity | x         | x        | x        |    | x  |    |    | x  |    | x  | x                   | x       | x   | x   | x   | x   | x                           |
| BILAG                                             | x         | x        | x        |    | x  |    |    | x  |    | x  | x                   | x       | x   | x   | x   | x   | x                           |

|                                                                     |   |   |     |     |     |     |     |     |     |     |     |     |     |     |     |

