### 2.1.4.2 TOXICOLOGY

The phase 1b PAVO (MMY1004) study evaluated subcutaneously administered daratumumab in combination with the recombinant human hyaluronidase PH20 enzyme (DARA-MD) in patients with relapsed or refractory MM. Patients received subcutaneous daratumumab according to the approved IV monotherapy dosing schedule at 1200 mg (n = 8) or 1800 mg (n = 45). The most common treatment-emergent adverse events with DARA-MD 1200 mg were thrombocytopenia, upper respiratory tract infection, insomnia, and decreased appetite (37.5% each). Anemia (33.3%), upper respiratory tract infection, pyrexia, and diarrhea (26.7% each) were the most common treatment-emergent adverse events with DARA-MD 1800 mg. One patient in the 1200-mg dose group (12.5%) and 11 patients in the 1800-mg dose group (24.4%) experienced infusion-related reactions, which were generally grade 1/2 and typically occurred at the first infusion. The 1800 mg dose achieved similar or greater serum concentrations compared with the 16 mg/kg IV dose [38]. In the phase 3 subcutaneous versus intravenous daratumumab study in multiple myeloma (COLUMBA), the most common grade 3 and 4 adverse events were anemia (34 [13%] of 260 patients evaluable for safety in the subcutaneous group and 36 [14%] of 258 patients in the intravenous group), neutropenia (34 [13%] and 20 [8%]), and thrombocytopenia (36 [14%] and 35 [14%]). Pneumonia was the only serious adverse event in more than 2% of patients (seven [3%] in the subcutaneous group and 11 [4%] in the intravenous group). There was one death resulting from a treatment-related adverse event in the subcutaneous daratumumab group (febrile neutropenia) and four in the intravenous group (sepsis [n=2], hepatitis B reactivation [n=1], and Pneumocystis jirovecii pneumonia [n=1])[37].

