#### **Infection or predisposition to infection**

15. has a history of, or ongoing, chronic or recurrent infection, including but not limited to, chronic renal infection, chronic chest infection (e.g. bronchiectasis), sinusitis, recurrent urinary tract infection (e.g. recurrent pyelonephritis), an open, draining, or infected skin wound, or an ulcer.
16. Evidence of latent tuberculosis (as documented by a positive QuantiFERON-TB test at screening, no findings on medical history or clinical examination consistent with active tuberculosis, and a normal chest radiograph) except for participants that are willing to complete at least 4 weeks of anti-tuberculosis therapy as per WHO or national guidelines prior to randomization and agree to complete the remainder of treatment while in the study.
17. has or has had a serious infection (e.g. sepsis, pneumonia or pyelonephritis) or has been hospitalized or received IV antibiotics for a serious infection during the 3 months prior to consent.
18. Ongoing infection (requiring antibiotic treatment or fever > 38°C), including known HIV, active or chronic hepatitis B or hepatitis C.
19. has experienced a recent single dermatomal herpes zoster eruption within the past 6 months, or has a history of disseminated forms of zoster within the past 2 years prior to Screening.
20. has a history of hepatitis B surface antigen (HBsAg) or hepatitis C antibody (anti-HCV) positive, or other clinically active liver disease, or tests positive for HbsAg or anti-HCV at Screening.
21. has a history of human immunodeficiency virus (HIV) antibody positive, or tests positive for HIV at Screening.
22. have had an opportunistic infection (e.g. pneumocystis, aspergillosis, mycobacterium avium complex).
23. has a SARS-CoV-2 Infection at screening or baseline, confirmed by a PCR test (a rapid test is mandatory before each visit; if this test is positive, then a PCR test must be performed).

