### 8.3 WITHDRAWAL FROM STUDY

A participant will be withdrawn from the study for any of the following reasons:

1. Withdrawal of consent to participate.
2. Lost to follow-up.
3. Death.
4. Subject is significantly non-compliant with study procedures, including inconsistent study drug dosing, which would put the subject at risk for continued participation in the trial as determined by the Investigator.
5. Enrollment in any other clinical study involving an investigational product or enrollment in any other type of medical research judged not to be scientifically or medically compatible with this study.
6. Decision by the investigator or sponsor in case of any adverse event that justifies withdrawal and is in the best interest of the subject. The following reasons automatically lead to the discontinuation of the study participation:
  - a. The Investigator believes it is in the best interest of the subject.
  - b. Subject develops an ECG change considered clinically significant.
  - c. The subject becomes pregnant.
  - d. The subject is diagnosed with a malignancy, with the exception of no more than 2 localized basal cell skin cancers that are treated with no evidence of recurrence or residual disease.
  - e. the subject is deemed ineligible according to the following TB criteria: A diagnosis of active TB is made or a subject undergoing evaluation has a chest

- radiograph with evidence of current active TB and/or a positive QuantiFERON®-TB test result, unless active TB can be ruled out.
- f. Subject develops a GI perforation.
  - g. If a diagnosis of deep vein thrombosis, pulmonary embolus, or non-cardiac, non-neurologic arterial thrombosis is confirmed.
  - h. Subject develops active neuropsychiatric SLE (excluding lupus headache) as defined by the CNS portion of SLEDAI-2K or BILAG.
  - i. HBcAb positivity with HBV DNA above the lower limit of quantification
  - j. Positive HIV test

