## 10.7 EVENTS OF SPECIAL INTEREST

The following AE are defined as AEs of special interest related to daratumumab:

- Injection related reactions (IRR)  $\geq$  Grade 3

- Infections  $\geq$  Grade 4
- Cytopenia (leukopenia, neutropenia, thrombocytopenia or anaemia)  $\geq$  Grade 4
- HBV-reactivation
- New malignancy

Toxicities are to be assessed according to NCI-CTCAE, Version 5.0. These events are to be considered serious only if they meet the definition of an SAE as shown in Section 10.1.3 (SERIOUS ADVERSE EVENTS).

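### Automatic withdrawal rule 8.3 6(i) depends on HBcAb and HBV DNA, but no planned test measures either marker

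*Protocol*

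**What the plan says.** Section 8.3, item 6, introduces its list with "The following reasons automatically lead to the discontinuation of the study participation", so the reasons that follow are mandatory. Item 6(i) is "HBcAb positivity with HBV DNA above the lower limit of quantification".

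The places that plan hepatitis testing read as follows:

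- Section 7.6.3 gives the viral panel as "Viral serology (HBsAg, anti-HBs, and HCV antibody").
- The core schedule, both at the front of the protocol and in 7.1.1, has a single row, "Viral Serology", marked at screening only. It names no markers.
- The LTE schedule has no viral serology row in either printing.
- Section 7.6 says that screening includes "HIV testing, hepatitis B, hepatitis C and TB tests", again without naming hepatitis B markers.
- Exclusion 20 in section 5.2 removes a patient with a history of HBsAg or anti-HCV positivity or other clinically active liver disease, or who "tests positive for HbsAg or anti-HCV at Screening".

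Section 10.7 lists "HBV-reactivation" as an event of special interest. Section 2.1.4.2 reports one treatment-related death from hepatitis B reactivation in the intravenous arm of the phase 3 myeloma trial.

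**The concern.** A mandatory stopping rule needs a measurement that can set it off. This one requires two results, core antibody and viral DNA, and the protocol plans neither.

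The patients at issue are those who pass screening. Exclusion 20 already removes anyone who tests HBsAg positive, so a rule built on core antibody plus DNA is aimed mainly at HBsAg-negative patients with past exposure. The named panel does not identify them. It includes anti-HBs, but no eligibility or withdrawal rule uses that result.

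Such a patient could receive eight doses of daratumumab, each preceded by 10 to 20 mg of dexamethasone (6.2.2), possibly on top of one background immunosuppressant and glucocorticoids. Detection of reactivation would then depend on an investigator choosing to order tests that the protocol does not plan. The protocol itself treats the risk as real, both by listing it in 10.7 and by citing a fatal case.

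**Working it through.** There is no stated figure to reproduce. The check compares every place in the protocol where hepatitis B testing or its markers appear.

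**Markers**

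| Place | HBsAg | anti-HBs | HBcAb | HBV DNA |
|---|---|---|---|---|
| 8.3, 6(i), withdrawal rule | no | no | required | required |
| 7.6.3, viral panel | yes | yes | no | no |
| 5.2, exclusion 20 | yes | no | no | no |
| 7.6, screening statement | unspecified | unspecified | unspecified | unspecified |
| Core schedule, both printings | generic row | generic row | not named | not named |
| LTE schedule, both printings | no row | no row | no row | no row |

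Of the 2 markers that 6(i) needs, 0 are named in 7.6.3 or in any schedule.

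**Timing**

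- Core visits are numbered 1 to 17, which is 17 visits.
- LTE visits after entry are numbered 18 to 25, which is 8 visits.
- Total: 17 + 8 = 25. Viral serology is marked at visit 1 only, so it is planned at 1 of 25 visits and at 0 of the remaining 24.

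**Can planned testing meet the rule?** It requires HBcAb positive and HBV DNA above the limit of quantification. Suppose, generously, that the unspecified hepatitis B test in 7.6 included HBcAb. The DNA half would still have no planned test at any visit, so the conjunction could not be reached through planned testing.

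**How many patients might be concerned?** The protocol gives no share of HBsAg-negative, anti-HBc-positive patients. With an assumed share p, independent patients and n = 10, the chance of enrolling at least one is 1 − (1 − p)^10:

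- p = 1%: 1 − 0.99^10 = 9.6%
- p = 5%: 1 − 0.95^10 = 40.1%
- p = 10%: 1 − 0.90^10 = 65.1%

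These are chances of enrolling a patient with past exposure. They are not chances of reactivation or of meeting 6(i), which also needs detectable DNA and would be lower.

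**The case against.** Four arguments can be made for leaving the text alone.

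1. *Section 7.6.3 is not a complete list.* HIV testing is required by 7.6 and used by exclusion 21, yet it is missing from the viral line in 7.6.3. Absence from that line does not prove that a test is not done, and the unspecified hepatitis B test in 7.6 leaves room for core antibody. This stands for HBcAb at screening. It does not help with HBV DNA, which no section plans.

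2. *Withdrawal rules need not have scheduled tests.* Malignancy, gastrointestinal perforation and thrombosis in the same list are event-driven, and the HIV rule, 6(j), also has no planned test after screening. This is fair as far as it goes. But those events present clinically, and the HIV rule has at least a planned screening test. Rule 6(i) is a purely laboratory criterion with no planned route at any visit.

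3. *Indirect safeguards exist.* ALT, AST and bilirubin are in the chemistry panel, which runs through the core study and every LTE visit. Grade 3 or higher toxicity requires the drug to be held (6.2.4), and exclusions 18 and 20 remove known or active hepatitis B. These limit the consequence. However, transaminases rise only once liver injury has begun, and the step from an abnormal value to an HBV test is left to discretion.

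4. *The Investigator's Brochure may give testing guidance.* It is not shown and cannot be judged. The mismatch within the protocol is certain. How many patients would be missed in practice is less so.

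**Conclusion.** The concern holds. HBcAb and HBV DNA appear only in 8.3 6(i), and no planned test can trigger that automatic rule. It can be met only by for-cause testing outside the schedule. The textual mismatch rests on no assumption.

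The practical size depends on the unstated share of HBsAg-negative, anti-HBc-positive patients in this population, and over the range shown it runs from a minor to a likely occurrence among 10 patients. Sample size, primary endpoint and efficacy analysis are not affected. It should be corrected because it concerns patient safety, the risk is one the protocol names itself, and the correction is cheap.

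**What to change.** - Add anti-HBc to the screening viral serology in 7.6.3 and name the markers in the schedule row.
- Test HBV DNA at screening in any anti-HBc-positive patient. If that patient is enrolled, repeat HBV DNA at set visits in the core and LTE periods, with a row in both schedules. Rule 6(i) can then stand as written.
- The alternative is to reword 6(i) in markers the trial measures. This is weaker, because those markers are also measured only at screening and would not detect later reactivation.

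The cost is one extra serology on screening blood already drawn from 10 patients, reflex and repeat HBV DNA tests in the few who are anti-HBc positive, and wording changes in 7.6.3 and the schedules (both printings).
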